#### Secondary outcomes: self-esteem, life satisfaction, and loneliness

Self-esteem will be measured using the Rosenberg self-esteem scale (SES). The SES consists of 10 items, with responses from 1 (completely agree) to 4 (completely disagree). The total score ranges from 10 to 40, higher scores indicating higher self-esteem. It was found to have a high reliability and validity [46]. For the 8th item (I wish I could have more respect for myself), in consideration of cultural difference, some studies suggest and prove that the way of expression should be changed to negative form when it is translated into Chinese [47,48].

Life satisfaction will be measured with the Life Satisfaction Index A (LSI-A), which has been proved having high reliability and validity [49]. LSI-A is consisted of 20 items for which an “agree” or “disagree” or “not sure” response is required. The total score ranges from 0 to 20, and higher total score indicates better life satisfaction.

Loneliness will be measured using the third edition of Russell’s UCLA Loneliness Scale which consists of 20 items, with responses from 1 (never) to 4 (often) [50]. The total score ranges from 20 to 80, with higher score indicating a higher sense of loneliness. According to the research of Russell (1996), the alpha coefficient was 0.89 and the test-retest reliability after twelve months was 0.73 among the elderly [51].

### Statistical analysis

According to some previous researches, personal characteristics of the subjects may have an impact on the outcomes. Though the RCT design is adopted, the demographic data between the control group and the experiment group still should be considered. When the two groups do not match on demographic data, related statistical methods will be brought in to make up for this. In addition, the data of participants who are absent from the group session for four times or more and who turn to antidepressant or other non-pharmaceutical intervention before the end of the therapy will be excluded when analyses conducted [39].

SPSS 16.0 statistical packages will be used to conduct the data analyses. Paired *t* test will be used to detect the changes of the outcome measures within intervention or control group. Standardized change scores will be calculated by subtracting pre-test score from post-test score of intervention and dividing by the SD for all participants combined. A repeated measures analysis of covariance (ANCOVA) model will be used to evaluate the effects of intervention on continuous outcome variables that are available at each data collection point. The between-subjects factor is group (intervention group, control group) and the within-subjects factor is assessment phase (baseline, post-test, follow-up test). All statistical tests were two sided, and *p* values < 0.05 were considered significant. In addition, effect sizes (Cohen’s d) [52] will be computed based on the differences between the pre-and post-intervention (or follow-up test) means and the pooled variance.

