**Methods:**

Sixty older adults (≥60 years of age) with mild to moderate depression will be randomly assigned to an experimental or a control condition. The participants in the experiment group will receive the reminiscence therapy under the Watt’s protocol with adaptation to Chinese Culture which consists of six weekly sessions of 90 minutes each. The control group will be treated as before. An assessor who is blind to intervention will conduct the measures before treatment, after treatment immediately, and three months after treatment.

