### Participants

A total of sixty subjects who fulfill the following inclusion and exclusion criteria will be recruited from the community.

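### Covariate adjustment depends on an observed demographic mismatch, with the method left open, instead of on a covariate set fixed in advance that includes baseline

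*Protocol article*

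**What the plan says.** All of this stands in the Statistical analysis section of the protocol article. It opens with the premise that "personal characteristics of the subjects may have an impact on the outcomes", and continues: "Though the RCT design is adopted, the demographic data between the control group and the experiment group still should be considered". The operative rule follows: "When the two groups do not match on demographic data, related statistical methods will be brought in to make up for this". The section does not list the demographic variables, define a mismatch, name the method or say when the comparison is made.

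For the main model it states: "A repeated measures analysis of covariance (ANCOVA) model will be used to evaluate the effects of intervention on continuous outcome variables". Group is the between-subjects factor, and "the within-subjects factor is assessment phase (baseline, post-test, follow-up test"). Despite the name ANCOVA, no covariate is given, and baseline is one of the repeated levels. The error criterion is "All statistical tests were two sided, and *p* values < 0.05 were considered significant". No other section fixes a covariate set.

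**The concern.** The premise and the rule do not fit together. If personal characteristics may influence the outcome, that is a reason to adjust for the influential ones whether or not they happen to be balanced. The article selects on imbalance instead. In a properly randomised trial, imbalance arises by chance and carries no information about prognosis. A prognostic variable that looks balanced stays out, and an irrelevant one that differs by chance goes in.

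At stake are precision, which is scarce with 60 participants, and a single defined model for the primary question. Because the variables, the criterion and the method are all open, several analyses of the Geriatric Depression Scale would be consistent with the text.

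**Working it through.** **Inputs.** From the article: 60 participants in total, two arms, two-sided 0.05. The article gives no power, effect size, SD, correlation or allocation ratio, so there is no stated figure to reproduce. Assumed: 30 per arm, outcome SD 1, effect 0.6 SD, pre-post correlation ρ of 0.5 to 0.7. No dropout is modelled.

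**1. How often chance sets off the trigger.** If a mismatch means p<0.05 on any of k independent variables, the probability is 1 − 0.95^k:
- k = 3: 14%
- k = 5: 1 − 0.774 = 23%
- k = 8: 34%
- k = 10: 40%

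**2. What the rule does to precision.** The group-by-phase model compares change from baseline. Simulated power for that contrast used five covariates, two of them prognostic (assumed correlations 0.4 and 0.3, acting equally before and after treatment):

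| ρ | Unadjusted | Imbalance rule | Prespecified demographics |
|---|---|---|---|
| 0.5 | 63% | 62% | 61% |
| 0.6 | 72% | 71% | 71% |
| 0.7 | 85% | 84% | 83% |

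The rule gains nothing. Fixed demographics gain nothing either, because stable effects largely cancel in a change score.

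**3. What the rule does to type I error.** With a mechanical p<0.05 trigger, post-test-only simulations (five covariates, R² 0.1 to 0.5) gave 3.8% to 4.4%, and the change contrast stayed near 5%. Taking the smaller p of the unadjusted and triggered analyses gave 5.2% to 5.7%. An unrestricted choice of the smallest p among unadjusted, triggered, all-covariate and single-covariate models gave 7.8% to 13.4%, which is an upper bound.

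**4. What a fixed baseline covariate gains.** The residual variance is 2(1 − ρ) for the change contrast and 1 − ρ² with baseline as covariate. The standard error is √(variance × 2/30), and power comes from the noncentral t distribution with 58 and 57 degrees of freedom.

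| ρ | Change: variance, SE, 0.6/SE | Power | Baseline covariate: variance, SE, 0.6/SE | Power |
|---|---|---|---|---|
| 0.5 | 1.00, 0.258, 2.32 | 63% | 0.75, 0.224, 2.68 | 75% |
| 0.6 | 0.80, 0.231, 2.60 | 72% | 0.64, 0.207, 2.90 | 81% |
| 0.7 | 0.60, 0.200, 3.00 | 84% | 0.51, 0.184, 3.25 | 89% |

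Simulation agrees within about a point (83% and 88% at ρ = 0.7). Adding two demographics to the baseline covariate changed power by about +3 points when they were strongly prognostic and ρ was 0.5, and by about −2 points when they were weakly or not prognostic.

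**The case against.** The strongest reply is that a journal article leaves the covariate list, the definition of mismatch and the method to a fuller document that is not shown, and that the sentence may describe a supplementary analysis. The first part stands for the missing detail. It does not reach the trigger itself: a later document could define the rule more closely, but adjustment would still depend on observed balance unless the rule were replaced. The second part is possible. The text does not say whether the adjusted analysis replaces or accompanies the main one, and that is itself part of the open choice.

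A reader might infer three stronger things, none of which the document supports.

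- *That omitting demographics costs about ten points of power.* A post-test-only simulation with correlations of 0.4 and 0.3 does show 63% under the rule against 74% with the two covariates fixed. The article's model uses baseline as a phase, however, and under its change contrast that gap disappears. Even post-test only, it shrinks to 63% against 66% at correlations of 0.25 and 0.2, and to none at 0.1 and 0.1.
- *That the rule inflates false positives.* Applied mechanically it does not. The higher rates need a free choice among models that the article does not itself propose.
- *That the decision is taken with outcome data in hand.* The article gives no timing. Baseline testing precedes the opening of the randomisation envelope (Design), so balance could be examined before any post-test.

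**Conclusion.** The point holds as a badly fixed rule. Adjustment triggered by chance mismatch contradicts the article's own reason for adjusting, adds no precision and leaves the choice of primary model open to the observed data. It does not invalidate the trial, and no inflation of type I error can be attributed to the rule as such.

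The gain available from replacing it comes mainly from using baseline as a covariate: about 12, 9 and 5 points of power at pre-post correlations of 0.5, 0.6 and 0.7. These figures rest on equal allocation, a 0.6 SD effect, complete data and one post-treatment comparison, none of which the article states. The share due to demographics is small and of uncertain sign.

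**What to change.** Delete the sentence that ties adjustment to mismatch. In its place, name before outcome data are seen a short covariate set to be used whatever the observed balance: the baseline value of the outcome being analysed, plus at most a few characteristics expected to be prognostic and known at entry. Age, sex and stable antidepressant use are examples; the article offers no evidence that these particular variables are prognostic, so the sponsor should justify the choice.

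Restructure the model to match: with baseline as a covariate, the within-subjects factor has two levels, post-test and follow-up. Baseline should not be both a covariate and an outcome level. Report baseline characteristics descriptively, without significance tests, and label any other adjustment as a sensitivity analysis.

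The cost is revised wording, this small change to the model and up to four degrees of freedom (baseline plus three characteristics) with 60 participants. Baseline scores are already collected, and age and antidepressant status are needed for the inclusion criteria; sex is a routine demographic item.

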### Intervention

#### Experiment group

The subjects who are arranged to the experiment group will be intervened using the reminiscence therapy manual proposed by Watt and Cappeliez (2000). According to the manual, the group consisted of six weekly sessions of 90 min each. There will be about four people in each subgroup. During each weekly session, the memories recalled focused on a different theme. The themes are as follows: major branching points in your life, family life, your career or major life work, your loves and hates, stress experiences, the meaning of your life and belief. Five relative questions were set to help retrieve memory in each theme. We explain to participants that the memories of these themes should be related to experiences with a significant impact on their life. Also, we make a distinction between personal recollections and recollections of historical facts which are not the focus of the intervention [25].

Except for the first session, the other sessions share the same procedures, including: homework review and agenda development (10 minutes), relaxation and focusing on reminiscence (5 minutes), contact work (50 minutes), feedback to clients (15 minutes), assignment of homework (5 minutes), feedback to therapist and questions (5 minutes). The first session will begin with participants’ self-introductions to get to know each other. The therapist will offer information about his work and qualifications to get confidence and closer to the participants. Then he will explain some concepts used in the session (such as “round”), rationale for reminiscence therapy, the preparations of the each intervention and corresponding procedures.

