#### Control group

The participants assigned to the waiting-list as control group will be treated as before. We will keep in touch with them getting to know whether they are still available to be the member of the control group.

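### The only stated analysis set drops participants for missed sessions and new treatment after randomisation, so the primary comparison is no longer between the groups as randomised

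*Protocol article*

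**What the plan says.** The rule is in the protocol article, Statistical analysis. It names "participants who are absent from the group session for four times or more and who turn to antidepressant" or some other non-drug help while therapy is still running, and says that their data "will be excluded when analyses conducted". The two conditions are joined by *and*. The rule is tied to no particular analysis or time point and is not described as per-protocol or as a sensitivity analysis. The article nowhere states an analysis of all randomised participants.

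Three other places matter:

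- **Design:** the randomisation envelope is opened after the baseline test, so before any session. Post-test and follow-up are planned for all participants.
- **Experiment group:** "the group consisted of six weekly sessions of 90 min each".
- **Design and Control group:** controls are on a waiting list and have no sessions.

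**The concern.** Randomisation protects the comparison only if membership of the analysis set does not depend on what happens after allocation. Here it does, and not in the same way in the two arms.

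- **Missed sessions.** Only therapy participants can meet this condition. That follows from the design and needs no assumption. If poor attenders tend to do worse, removing them flatters the therapy.
- **New treatment.** This can occur in either arm. Participants are not described as blind, and people on a waiting list may have more reason to seek help elsewhere, so equal rates cannot be assumed. If the controls who seek help are those getting worse, removing them makes the control arm look better and works against the therapy.

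The rule is also uneven over time. A person who meets it during the six weeks is lost from the three-month comparison too, whereas a person who starts an antidepressant after therapy ends is kept.

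The article's own reasoning makes a link to outcome plausible. The Discussion cites a study proposing that people with a more favourable attitude to reminiscence gain more, and it plans to examine engagement as an influence on the effect. The Background partly blames earlier inconsistent findings on high dropout and on studies that were not randomised. Excluding the least engaged from one arm works against the aim of improving on those studies.

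**Working it through.** The article gives no power calculation, SD or expected exclusion rate, so there is no figure to reproduce. The steps below settle the logic first and then illustrate the size.

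**1. The two readings of *and***

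| Reading | Therapy participant excluded if | Control excluded if |
|---|---|---|
| Both conditions required | at least 4 of 6 sessions missed and new treatment started | never (no sessions to miss) |
| Either condition suffices | at least 4 of 6 missed, or new treatment started | new treatment started |

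On the first reading only one arm can lose participants. On the second, one trigger is still confined to one arm. Neither leaves the randomised groups intact.

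**2. Size by formula**

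From the article: 60 randomised, two-sided tests at 0.05. Assumed: 30 per arm (the allocation ratio is not stated), unit SD, no true effect, exclusions from the therapy arm only. A fraction *p* of that arm is excluded, and their mean outcome is *D* SD worse than that of those retained.

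If the whole arm has mean 0 and the retained have mean *m*, then (1 − p)m + p(m + D) = 0, so m = −pD. The spurious benefit is therefore p × D.

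SE = √(1/n_retained + 1/30). Type I error = Φ(−1.96 + pD/SE) + Φ(−1.96 − pD/SE).

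| p (excluded) | D | Bias (SD) | SE | Bias/SE | Type I error |
|---|---|---|---|---|---|
| 2/30 (2) | 0.5 | 0.033 | 0.263 | 0.127 | 5.2% |
| 2/30 (2) | 0.8 | 0.053 | 0.263 | 0.203 | 5.5% |
| 20% (6) | 0.5 | 0.10 | 0.274 | 0.365 | 6.5% |
| 20% (6) | 0.8 | 0.16 | 0.274 | 0.584 | 9.0% |
| 30% (9) | 0.8 | 0.24 | 0.285 | 0.844 | 13.5% |

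**3. Size by simulation**

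40,000 trials per scenario, two-sample t test, no true effect, 30 per arm. Exclusion depends on a latent tendency with correlation ρ to a worse outcome.

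| Excluded, therapy / control | ρ | Bias | Type I error |
|---|---|---|---|
| none | – | 0.00 | 4.8% |
| 10% / 0 | 0.3 to 0.5 | 0.06 to 0.10 SD for therapy | 5.4% to 6.3% |
| 20% / 0 | 0.3 to 0.5 | 0.10 to 0.18 SD for therapy | 6.6% to 9.6% |
| 30% / 0 | 0.3 to 0.5 | 0.15 to 0.25 SD for therapy | 8.0% to 13.8% |
| 20% / 10% | 0.5 | 0.08 SD for therapy | 5.9% |
| 20% / 20% | 0.5 | about 0 | 5.1% |
| 0 / 20% | 0.5 | 0.17 SD against therapy | 9.6% |

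The 4.8% in the first row is the nominal 5% within simulation error (standard error √(0.05 × 0.95/40,000) = 0.11 percentage points).

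**4. Power**

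Power = Φ(d/SE − 1.96). At an assumed d of 0.5 it is 49.1% with 30 vs 30, 44.7% with 24 vs 30 and 42.0% with 21 vs 30.

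**The case against.** The strongest reply is that the damage may be small. An exclusion criterion already screens out people who cannot commit to weekly attendance, and the threshold is four absences out of six. If both conditions are required, exclusions would probably be rare, and rates of 20–30% are realistic only on the either/or reading. With two exclusions the type I error is barely above 5%. If the same mechanism removes equal fractions from both arms, the bias nearly cancels. This stands, and it is why the low and balanced cases are shown. But cancellation cannot be counted on when one trigger exists in one arm only.

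Second, the formula and the simulation treat the outcome as a single standardised measure, while the plan is a repeated-measures ANCOVA that includes baseline. If excluded participants were already worse at entry, the group-by-phase contrast would remove part of the difference. This also stands: the figures show scale and are not this trial's error rate.

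Third, why people miss sessions or seek other help is conjecture, and absence may have unrelated causes. True, but the analysis should not depend on guessing the reasons. The article's offer to adjust when demographics do not match would not repair selection driven by symptoms or engagement.

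Fourth, a separate analysis plan might add an all-randomised analysis. It might, but the exclusion is fixed in this article and is not a detail left open. The reference cited in support of the rule shows at most a precedent.

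The Control group section says that staff will keep in touch with controls, "getting to know whether they are still available to be the member of the control group". It states no exclusion from analysis, and no weight is placed on it here.

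**Conclusion.** The concern holds and must be fixed. As written, the primary GDS comparison rests on a set defined by post-randomisation events, at least one of which can occur in only one arm. This conclusion comes from the design and holds on either reading of *and*; it does not depend on the illustrative figures.

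The size is unknown because exclusion rates and their relation to outcome are not given. Under the assumptions stated above, therapy-arm exclusions alone give a spurious benefit from about 0.03 SD (type I error 5.2%) to about 0.25 SD (13.8%). Control-only exclusions of 20% give 0.17 SD in the opposite direction. The net direction cannot be predicted.

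**What to change.** Replace the exclusion sentence in Statistical analysis with wording such as:

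> The primary analysis includes all randomised participants in the arm assigned, whatever their attendance or use of other treatment. Post-test and follow-up measures are sought from everyone.

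Then:

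- Keep the set without four or more absences and without new treatment as a secondary sensitivity analysis, labelled as such and reported beside the primary result. State whether either condition suffices or both are needed.
- Tabulate absences of four or more and new treatment by arm.
- Make sure the fitted model does not discard people with one missing visit, since those who stop attending are the most likely to miss assessments. A conventional repeated-measures ANCOVA on complete cases could lose the same people again; a likelihood-based repeated-measures model that uses all available visits would not do so for this reason.

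The cost is mainly wording. Assessments are already scheduled for all participants, so the extra work is following up those who stop attending and specifying how missing outcomes are handled. The estimated effect may be slightly smaller.

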#### Inclusion criteria

1) The age of participants is equal or over than 60 years old;

2) The score of the Geriatric Depression Scale (GDS) should fall between 10 and 26 points;

3) A score of 24 or higher on the Mini-Mental State Examination (MMSE);

4) Not taking anti-depressant medication or taking part in other psychotherapy when enrolling, or with stable anti-depressant medication for at least three months;

5) Having no problem with communication (such as, can speak fluent mandarin, or, his/her dialect can be understood by other participants or evaluators).

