### Data collection and outcome measures

The main data will be collected using some standardized instruments with demonstrated validity and reliability which will be described as follows. Data collection will occur on screening (as for baseline or pre-test), after intervention immediately (as for post-test), and three months after the intervention (as for follow-up). In addition to these measures, we will use some scales developed by ourselves to collect data. These scales are used to assess the participants’ attitude towards the intervention. Moreover, the therapist will be given the scales used to rate participants’ compliance after each session.

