#### Primary outcome: Depressive symptoms

Symptoms of depression will be measured with the GDS. GDS is a self-rated scale consisting of 30 items with response of “yes” or “no” to measure a person’s emotional state in the past week. The entire scores ranges from 0 to 30, and higher scores represent more severe level of depression. Generally, scores from 11 to 20, from 21 to 30 indicate mild, severe depression respectively [44]. The GDS designed specifically for the elderly, and it has been proved with high reliability and validity. According to the research of Yesavage and Brink (1982), the Cronbach’s alpha coefficient was 0.94 and the test-retest reliability after one week was 0.85 among twenty participants [45].

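### The only Cohen's d defined is a before-after contrast without a between-group term, and the within-arm paired t tests are not labelled descriptive, although the GDS baseline is also the selection score

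*Protocol article*

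**What the plan says.** Four parts of the protocol article bear on this point.

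- **Selection.** Inclusion criteria: "The score of the Geriatric Depression Scale (GDS) should fall between 10 and 26 points".
- **Baseline.** Data collection and outcome measures: "Data collection will occur on screening (as for baseline or pre-test"). The article describes no second baseline after selection. The GDS is also the primary outcome.
- **Within-arm quantities.** Statistical analysis: paired t tests "will be used to detect the changes of the outcome measures within intervention or control group", and Cohen's d "computed based on the differences between the pre-and post-intervention (or follow-up test) means and the pooled variance". The d sentence names no group term.
- **Between-group model.** The same section says that a repeated measures ANCOVA "model will be used to evaluate the effects of intervention on continuous outcome variables that are available at each data collection point", and specifies: "The between-subjects factor is group (intervention group, control group) and the within-subjects factor is assessment phase (baseline, post-test, follow-up test").

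All tests are two-sided at 0.05. Under Study purposes, the first aim is a comparison with the control group. The second aim names only the experiment group.

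**The concern.** People are admitted because of a GDS score, and change is then measured from that same score. Part of any high score is temporary, so the group mean is expected to fall at retest whatever treatment is given. Natural recovery may add to this. A within-arm test and a pre-post effect size contain both components together with any treatment effect, and cannot separate them.

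What is at stake is mainly the effect size. As worded, the only d in the plan does not measure the first aim, which is therapy against control. In a 60-person trial, d is a figure that readers and later meta-analyses are likely to take up, and a sound p-value from the group model does not correct it. The paired tests matter less. Still, with no descriptive label, and with a second aim worded for the experiment group alone, they can be mistaken for evidence of efficacy.

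**Working it through.** The article gives no effect size, SD or power figure, so there is nothing of its own to reproduce. The check asks how large the two within-arm quantities are when the therapy has no effect.

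**Inputs from the article.** GDS range 0 to 30; eligibility 10 to 26; screening score used as baseline; 60 participants; two-sided 0.05. On reliability it says "the test-retest reliability after one week was 0.85 among twenty participants". That is a favourable value here, because post-test follows a six-week intervention and follow-up comes three months after that.

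**Assumptions not in the article.** Source-population GDS mean 7, 10 or 12; SD 5 or 6; normal scores; 30 per arm (no ratio is stated); retest correlation r of 0.85, with 0.7 and 0.5 as alternatives for the longer interval.

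**Formulas.** Expected fall ≈ (1 − r) × (mean of those selected − population mean). Pre-post d = fall ÷ √[(pre variance + post variance) ÷ 2]. Rejection rates come from simulation: true score plus independent error, rounded and clipped to 0–30, 3,000 null trials per scenario.

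**Worked case.** Mean 7, SD 5, r = 0.85: the mean of those selected is 12.705, so the fall is 0.15 × (12.705 − 7) = 0.86. The simulation gives 0.88.

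All scenarios at r = 0.85, no treatment effect:

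| Population mean, SD | Formula fall | Simulated fall | Pre-post d | One-arm paired test significant | Between-arm test significant (change / baseline-adjusted) |
|---|---|---|---|---|---|
| 7, 5 | 0.15 × 5.705 = 0.86 | 0.88 | 0.29 | 40.7% | 5.1% / 5.2% |
| 7, 6 | 0.15 × 6.485 = 0.97 | 0.99 | 0.27 | 38.7% | 5.9% / 5.7% |
| 10, 5 | 0.15 × 3.681 = 0.55 | 0.57 | 0.17 | 19.8% | 5.0% / 4.7% |
| 10, 6 | 0.15 × 4.407 = 0.66 | 0.68 | 0.17 | 19.9% | 5.2% / 5.2% |
| 12, 5 | 0.15 × 2.522 = 0.38 | 0.38 | 0.10 | 11.6% | 5.0% / 5.2% |
| 12, 6 | 0.15 × 3.166 = 0.47 | 0.49 | 0.12 | 12.6% | 5.1% / 5.5% |

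**Lower correlation.** At r = 0.7 the fall is 0.8 to 1.9 points, d 0.20 to 0.52, and one-arm significance 19% to 70%. At r = 0.5 the figures are 1.3 to 3.2 points, 0.31 to 0.78, and 29% to 92%.

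**Between-arm comparison.** Over all 18 scenarios, the two-sample t test on change and the baseline-adjusted comparison rejected in 4.4% to 5.9% of null trials, consistent with 5%. With two visits, the t test on change is the group-by-phase test. The three-visit model itself was not simulated.

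**Standardiser.** The eligibility window narrows the baseline SD: at r = 0.85 it is 2.57 to 3.84 in those selected, against 5 or 6 in the population. In the worked case, dividing by the baseline SD alone gives 0.880 ÷ 2.569 = 0.34 instead of 0.29. The choice of SD therefore has to be stated.

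**The case against.** The strongest reply is that the plan already assigns the evaluation of intervention effects to a model with group as a between-subjects factor. In a randomized trial, regression to the mean is equal in expectation in both arms and cancels there, as the simulation confirms. The paired tests are described only as detecting change within an arm. Cohen's d appears last, as an addition, and if it were shown for both arms the control value would make the regression visible. The sizes above also depend on population figures that the article does not give.

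Most of this stands, and it rules out several stronger readings:

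- A reader might infer that the within-arm tests are the efficacy tests, so that regression to the mean will be reported as a treatment effect. The article does not say so. Nor does it plan to contrast a significant result in one arm with a non-significant one in the other. Such a rule would err in 7% to 26% of null trials over the scenarios here, but it is not in the plan.
- A reader might see a contradiction in the two standardisers, the SD of all participants combined and the pooled variance. They belong to two different statistics, standardized change scores and d, so there is none.
- A reader might extend the selection argument to every outcome. Selection is on GDS only. Self-esteem, life satisfaction and loneliness are affected only through their correlation with GDS and through natural course.

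Two things remain. The group model protects its own p-value, not a d computed from before-after means. And the content of d is not simply left to an unseen analysis plan: the article states what it is built from, and a between-group difference is not part of that statement.

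**Conclusion.** The point holds as an inexpensive improvement to the effect-size definition and to the status of the paired tests. It is not a flaw in the planned test of efficacy, which is between groups.

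Followed as written, the GDS d includes regression to the mean and natural course. At the stated reliability of 0.85, regression alone contributes a fall of 0.4 to 1.0 GDS points and a d of 0.10 to 0.29, with a one-arm paired test significant in 12% to 41% of trials, all with no treatment effect. These figures rest on an assumed source-population mean of 7 to 12, SD 5 to 6, normal scores and 30 per arm. They rise if the correlation over the real interval is below the one-week value. Natural course is not included in them.

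**What to change.** Change the wording of the Statistical analysis section in three places:

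1. Define Cohen's d as the baseline-adjusted difference between arms at post-test, and likewise at follow-up, divided by one named SD, with a 95% CI. The pooled within-arm baseline SD is one option; if it is chosen, note that the eligibility window narrows it for GDS.
2. Label the paired t tests and all within-arm changes as descriptive.
3. State that conclusions on efficacy, for both aims, rest on the between-arm contrast, and name it: the group-by-phase term or the baseline-adjusted group difference.

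No data collection or sample size changes. The cost is that the reported effect size will probably be smaller than a pre-post d.
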